### Who will take informed consent? {26a}

During the preoperative visit, on the patient’s arrival in the hospital department on the day before surgery, the investigating physician will screen the patient for eligibility to participate, invite the patient to take part in the study and hand out the patient information leaflet, outline the trial (objectives, benefits, and constraints for the patient), and check that the NRS has been understood in order to evaluate postoperative pain. This NRS is routinely presented to all patients undergoing a surgical procedure.

On the day of the procedure, the investigating physician will collect the signed consent form after ensuring that the patient has understood the information leaflet, and recheck the inclusion and non-inclusion criteria.

Randomization will be carried out using the electronic case report form (eCRF) module (allocation of the randomization group and number), and presurgical data will be entered in the eCRF.

### Additional consent provisions for collection and use of participant data and biological specimens {26b}

This trial does not involve collecting biological specimens for storage.

### Interventions

#### Explanation for the choice of comparators {6b}

Patients will be randomly allocated to either the intervention group (ANI) or the control group (standard care only). Standard care was chosen as an appropriate comparator given that the intervention is proposed as an adjunct to routine care. Indeed, there is to date no recommendation for routine intraoperative analgesia monitoring.

#### Intervention description {11a}

In the control group, patients will receive general anesthesia with propofol, ketamine, and remifentanil (use of neuromuscular blocking agent left to the discretion of the investigator) for induction and desflurane and remifentanil (with or without neuromuscular blocking agent) for maintenance of anesthesia. Anesthetic drug dosing and administration will be left to the discretion of the investigator. Intraoperative Analgesia/Nociception Index (ANI) will be monitored; however, data will not accessible to the investigator but will be stored in the monitor intern memory for further analysis.

In the experimental (ANI) group, patients will receive general anesthesia with propofol, ketamine, and remifentanil (with or without neuromuscular blocking agent) for induction and desflurane and remifentanil for maintenance with a specific algorithm (Fig. 1—study protocol diagram). The administration of remifentanil will be goal-directed by ANI, as well as the prophylactic injection of morphine at the end of surgery.

**Fig. 1 Fig1:**
[figure not shown]
Study protocol diagram

#### Criteria for discontinuing or modifying allocated interventions {11b}

All patients may leave the study at any time for any reason if they wish to do so without any consequences. Interventions will be discontinued if there are abundant adverse events (AEs) or serious adverse events (SAEs).

#### Strategies to improve adherence to interventions {11c}

Since patients in the ANI group will be on general anesthesia during the study, no specific strategy to improve adherence to intervention will be needed.

#### Relevant concomitant care permitted or prohibited during the trial {11d}

Authorized medicinal products are those normally used during general anesthesia. The patient’s routine treatments (antiplatelet drugs, β-blockers, and other antihypertensives, statins, etc.) will be managed in accordance with the current recommendations and the principles of good clinical practice. The following drugs are authorized within the scope of this trial: local anesthetics (levobupivacaine and ropivacaine), analgesics (ketoprofen, nefopam, paracetamol, tramadol), antiemetics (dexamethasone, droperidol, ondansetron), neuromuscular blocking agents (cisatracurium, succinylcholine), narcotics (desflurane, ketamine, propofol), and opioids (morphine, remifentanil).

The ANI calculation can be changed over 5 to 10 min following the administration of drugs affecting sinus cardiac activity (atropine, ephedrine, and phenylephrine mainly in the surgical context). If one or more of these drugs must be administered in the form of a bolus, this will be entered in the electronic case report form (eCRF), and the remifentanil dose will be maintained for the next 10 min without considering variations in ANI.

The continuous administration of vasopressors (ephedrine, phenylephrine, or noradrenaline) is prohibited during the study. If one or more of these drugs must be administered in the form of a bolus, this will exclude the patient from the study.

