Variations in ANI reflect the changes in nociceptive stimulation during general anesthesia combining various narcotic (propofol, sevoflurane, or desflurane) and analgesic (fentanyl, sufentanil, and remifentanil) agents [5, 10–12]. The target ANI range value during general anesthesia is 50 to 80 in order to optimize the intraoperative administration of opioids, in particular, remifentanil [9].

Given its extremely rapid pharmacokinetic and pharmacodynamic properties (length of time to onset < 1 min and duration of action < 10 min), remifentanil, which has already been used in our earlier ANI studies, appears to be an analgesic agent that is particularly suitable for continuous monitoring of the nociception/antinociception balance [5, 9, 13–15]. However, the use of high doses of remifentanil may lead to the risk of chronic pain, which can be partly prevented by the administration of ketamine, or cause hypotension or intraoperative bradycardia warranting optimization of the intraoperative administration of this drug [16, 17].

In a previous study, we have highlighted the good performance of ANI recorded at the arrival in PACU for the assessment of immediate postoperative pain [14]. The area under the receiver operating characteristics curve (ROC AUC) was 0.86, with 78% sensitivity and 80% specificity to detect patients with moderate to severe pain, assessed with the Numerical Rating Scale (NRS) > 3.

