### Eligibility criteria {10}

Participants meeting the following criteria will be included: Adult patients undergoing elective surgery involving general anesthesia with intubation, having an *American Society of Anesthesiologists* (ASA) score of I to III, who have given their consent according to the methods described in article L1122-1-1 of the French Public Health Code, and affiliated to a social security scheme or benefiting from such a scheme.

Participants meeting one or more of the following criteria will be excluded: age under 18 years, elderly patients aged over 75 years [21], general anesthesia without intubation (laryngeal mask), intraoperative local anesthesia with neuraxial block (peridural or spinal block), opioid-free anesthesia, arrhythmia or presence of a pacemaker, outpatient surgery, cardiac or cerebral surgery, obstetric surgery (Cesarean section), surgery performed with local neuraxial or peripheral anesthesia alone, surgery performed in prone position, emergency surgery, endoscopic procedure or interventional radiology, chronic pain treated by opioids, surgery scheduled to take less than 1 h, autonomous nervous system disorder (epilepsy, history of transient ischemic attack or stroke, paraplegia, hemiplegia, orthostatic hypotension, dysautonomia), patient suffering from cardiogenic or septic shock, continuous perfusion of vasoactive agents (ephedrine, phenylephrine, adrenaline or noradrenaline), scheduled postoperative transfer to ICU (patient intubated) after surgery, person under guardianship or curatorship, pregnancy, and breastfeeding.

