#### Sample size {14}

Given the fact that immediate postoperative pain can affect 30% of patients [1], a total of 161 patients per group (322 patients) will give 90% power using a bilateral test with a *p* value of 5% to detect a 50% reduction in the incidence of immediate postoperative pain (NRS ≤ 3) in patients guided by ANI. Given the specific features of this protocol (essentially the direct transfer from operating theater to continuous monitoring or ICU, use of continuous vasopressors), the final decision is to include a total of 380 patients (190 per group). An interim analysis will be scheduled halfway through the enrolment period (95 patients per group). The *p* value used to decide withdrawal from the trial on efficacy grounds is set at 0.003 (correction of the O’Brien-Fleming alpha-spending function).

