### Assignment of interventions: allocation

#### Sequence generation {16a}

Randomization will be performed over the REDCap^®^ website (https://redcap.chu-clermontferrand.fr) to allow immediate allocation. The randomization list is balanced by blocks of variable and undisclosed size and stratified per center and per type of surgery. Patients will be randomized at day 0, after written informed consent is obtained and just before surgery. Each patient will be given a unique patient number and a unique randomization number. It is not possible to change group after randomization.

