### Assignment of interventions: blinding

#### Who will be blinded {17a}

Physicians and anesthetic nurses in the theater room cannot be blinded for the randomized arm. Physicians, nurses in PACU and in the surgical ward, and patients will be kept blinded for the randomized arm. Data analysts will be blinded for the randomized arm. Outcomes are mainly objective abstracted from electronic data to reduce bias.

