## Statistical methods

### Statistical methods for primary and secondary outcomes {20a}

The main analysis will take the form of an intent-to-treat procedure using the Stata^®^ (version 13, StataCorp, College Station) and R (http://cran.r-project.org/) software; all of the statistical tests will be carried out with an α value of 5%. The continuous variables will be presented as mean and standard deviation, provided that distribution is normal (Shapiro-Wilk test, if required). In the event of an anomaly, they will be presented as median, quartiles, and ranges. Qualitative variables will be expressed in numbers and related percentages. Where feasible, graphs will accompany these analyses. Intergroup comparisons will be routinely carried out (1) without adjustment (2) by adjusting factors, the distribution of which might not be balanced between the groups, despite randomization.

The patients will be described and compared between the groups at baseline, according to the following variables: compliance with eligibility criteria, epidemiological characteristics, clinical characteristics, and possible treatments. The initial comparability of both arms will be assessed on the basis of the principal characteristics of participants and potential factors linked to the primary endpoint. Any difference between the two groups in terms of one of these characteristics will be determined based on clinical as opposed to purely statistical considerations. Protocol deviations, patients distributed according to these deviations, and reasons for withdrawal will also be described. The number of patients enrolled and the enrolment graph will be presented per group.

Since a 50% reduction in the incidence of immediate postoperative pain in PACU patients receiving ANI-directed intraoperative analgesia ranging from 50 to 80 must be highlighted, the primary endpoint (percentage of patients with NRS > 3) will be compared using the *x*^2^ paired test or Fisher’s exact test, if applicable.

Secondly, this analysis can be completed in a multivariate situation using a generalized, linear mixed model approach to logistics, considering inter- and intra-site variability. The covariables will be considered in terms of clinical relevance (other treatments, continuous use of vasopressors, type of surgery) and the results of previous univariate analyses. The results will be expressed in terms of related odds ratios and 95% confidence intervals.

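### The protocol gives two opposite rules for an ephedrine or phenylephrine bolus, and the rule that excludes the patient acts after randomisation and conflicts with intention to treat

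*Protocol article*

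**What the plan says.** The section on concomitant care {11d} deals with vasoactive drugs in two consecutive paragraphs.

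- The first concerns drugs that disturb the ANI signal: atropine, ephedrine and phenylephrine. If one is given as a bolus, "this will be entered in the electronic case report form (eCRF), and the remifentanil dose will be maintained for the next 10 min", whatever the ANI shows. The patient stays in the trial.
- The second prohibits continuous ephedrine, phenylephrine or noradrenaline, and then adds: "If one or more of these drugs must be administered in the form of a bolus, this will exclude the patient from the study".

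Other sections bear on what happens to these patients:

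- **Sequence generation {16a}:** "Patients will be randomized at day 0, after written informed consent is obtained and just before surgery".
- **Who will be blinded {17a}:** "Physicians and anesthetic nurses in the theater room cannot be blinded for the randomized arm".
- **Eligibility criteria {10}:** continuous infusion of vasoactive agents is already a reason for non-inclusion.
- **Sample size {14}:** 161 per group is raised to 190 because of features of the protocol, "essentially the direct transfer from operating theater to continuous monitoring or ICU, use of continuous vasopressors".
- **Statistical methods {20a} and {20c}:** the analysis is by intention to treat, with no stated exception. {20a} also names continuous vasopressor use as a candidate covariable for the multivariable model of the primary endpoint.

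**The concern.** Ephedrine and phenylephrine are on both lists, so the same event in theatre has two incompatible consequences. One site could keep the patient and another could exclude the patient, and both would be following the text.

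The exclusion rule is also a problem in itself. A bolus or infusion during surgery comes after randomisation. The staff who decide to give it know the arm. The need for it may also depend on the arm: the background {6a} says that high doses of remifentanil may "cause hypotension or intraoperative bradycardia warranting optimization of the intraoperative administration of this drug", remifentanil titration is one of the two things that differ between the arms (the other is ANI-triggered morphine), and better intraoperative haemodynamics is a secondary objective. If patients leave the primary comparison because of such an event, randomisation no longer fully protects it.

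**Working it through.** **1. The two rules side by side**

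| Drug given as bolus | First paragraph | Second paragraph |
|---|---|---|
| Atropine | record, hold remifentanil, continue | not covered |
| Ephedrine | record, hold remifentanil, continue | exclude |
| Phenylephrine | record, hold remifentanil, continue | exclude |
| Noradrenaline | not covered | exclude |

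The contradiction is confined to ephedrine and phenylephrine.

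**2. Is it a slip?** Probably. The sentence just before it prohibits continuous administration, and {10}, {14} and {20a} mention only continuous use. If infusion is substituted for bolus, the contradiction goes. The exclusion still follows randomisation, and it still conflicts with {20a} and {20c}.

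**3. The plan's own sample size.** Inputs from {14}: 30% against 15%, two-sided 5%, 90% power. With pooled variance and p̄ = 0.225:

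n = [1.960·√(2·0.225·0.775) + 1.282·√(0.30·0.70 + 0.15·0.85)]² / 0.15² = 160.8, so 161 per group.

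This matches the plan. The allowance in 190 per group is 1 − 161/190 = 15.3%.

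**4. Power if patients are removed.** The exclusion rates are assumptions, because the protocol gives none.

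Power = Φ{[0.15·√n − 1.960·√(2·0.225·0.775)] / √(0.30·0.70 + 0.15·0.85)}

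| Excluded | n per group | Power |
|---|---|---|
| 0% | 190 | 94.1% |
| 5% | 180.5 | 93.0% |
| 10% | 171 | 91.7% |
| 15.3% | 161 | 90.0% |
| 20% | 152 | 88.3% |
| 30% | 133 | 83.8% |

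**5. Bias with no true effect.** Assume 30% pain in both arms, 20% of controls excluded (n = 152) and 10% of the ANI arm excluded (n = 171). Assume also that the 20% of patients who would be excluded under control care have a different pain risk, and that half of them escape exclusion in the ANI arm.

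- Risk 20% in those patients. Never-excluded risk = (0.30 − 0.20·0.20)/0.80 = 32.5%. Retained: control 32.5%, ANI (0.80·0.325 + 0.10·0.20)/0.90 = 31.1%. Difference 1.4 points in favour of ANI, rejection probability 5.8%.
- Risk 40% in those patients. Never-excluded risk = (0.30 − 0.20·0.40)/0.80 = 27.5%. Retained: control 27.5%, ANI (0.80·0.275 + 0.10·0.40)/0.90 = 28.9%. Difference 1.4 points against ANI, rejection probability 5.9%.

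This is not an upper bound. Suppose 40% of controls and 20% of the ANI arm are excluded, with 15% pain among the excluded in each arm. Retained risks are (0.30 − 0.40·0.15)/0.60 = 40.0% and (0.30 − 0.20·0.15)/0.80 = 33.8%, a spurious 6.2 points. With n = 114 and 152, the rejection probability is about 18%. If excluded patients have the same 30% risk as the rest, the bias is zero.

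**The case against.** The strongest reply is that the conflict with intention to treat is inferred. The sentence excludes a patient from the study but does not say that the data leave the primary analysis. Intention to treat is stated twice, {20a} promises a description of deviations and withdrawals, and detailed analysis sets belong in an analysis plan that is not shown. The extra patients in {14} can be read as an allowance for those who bypass PACU and so have no PACU pain score, which is compatible with intention to treat. The contradiction is probably a one-word slip, sites work from the full protocol, and every bias figure rests on assumed rates.

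Much of this is fair, and it narrows the supporting points. The sample-size section does not prove that these patients would be dropped. The covariable in {20a} is not dated, so it need not be an intraoperative event. The 94% power for 190 per group is an upper bound, because some patients will have no PACU score.

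The central point stands. The criticism is of a rule the document states, not of a missing detail. Exclusion from the study for an event after randomisation contradicts an intention-to-treat analysis without exceptions. Reading the sentence as a slip removes the clash between the two bolus rules but not this one.

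**Conclusion.** The concern holds and should be fixed. The text gives ephedrine and phenylephrine boluses two incompatible consequences. The exclusion, whether for a bolus or for an infusion, comes after randomisation, is triggered by unblinded staff and conflicts with the stated intention-to-treat analysis.

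Confidence is high on the text and low on the numerical effect. The protocol gives no rate of bolus or infusion, so the direction of any bias is unknown. Under moderate assumptions it is small and the loss of power is within the planned allowance; with frequent and unequal exclusion it could be material. The case for action is that the risk is avoidable at little cost.

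**What to change.** - Delete or correct the bolus-exclusion sentence in {11d}, and keep the rule of recording the bolus and holding remifentanil for 10 minutes.
- State that any vasopressor bolus or infusion after randomisation is a recorded protocol deviation and not an exclusion.
- Collect the PACU pain score in these patients and analyse all randomised patients by intention to treat. Handle those who bypass PACU under the missing-data plan in {20c}.
- Keep any analysis without vasopressor patients as a per-protocol sensitivity analysis only.

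The cost is one corrected sentence, one sentence on analysis status and a notice to sites, with ethics review if the amendment is classed as substantial under {25}. Enrolment is under way, so scores never collected from patients already excluded may not be recoverable, and their number should be reported.

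No extra patients are needed. With 190 per group and complete scores, power is 94.1% at the design effect. Keeping everyone may dilute the effect. If 10% of the ANI arm gains no benefit (assumed), its risk is 0.10·0.30 + 0.90·0.15 = 16.5% and power is 87.9%. At 15% it is 0.15·0.30 + 0.85·0.15 = 17.25% and 83.6%.

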#### Provisions for post-trial care {30}

This study will not include any ancillary or post-trial care. There is no compensation budget item for this study.

### Outcomes {12}

The primary outcome is the immediate postoperative pain in PACU defined by an NRS > 3 during PACU stay. The secondary outcomes are as follows:
Maximum pain score on the first day after surgery (0 to 10 rating scale). The NRS will be assessed every 6 h for the first 24 h (T0 = time of arrival in the PACU).Overall pain management satisfaction score on day 1 after surgery (0–10 NRS).Morphine dose level in PACU (mg).Postoperative nausea and vomiting in PACU.Total dose of morphine administered on the first day after surgery (mg).Duration of PACU stay (time taken to obtain an Aldrete score ≥ 9) (min) [22].Patient destination after surgery (surgical unit, follow-up care, ICU).Incidence of postoperative complications on the first and seventh day after surgery for hospitalized patients using the *Post-Operative Morbidity Survey* (POMS) (Annex 1) [23].Duration of hospital stay (days).Mortality at 28 days.

#### Participant timeline {13}

The participant timeline is shown in Table 1.

**Table 1 Tab1:** Participant timeline

Time point**	Study period						
	Enrollment	Allocation	Post-allocation				Close-out
	D-1	D0	D0	D1	D7	D28	D28
**Enrollment**							
**Eligibility screen**	X						
**Informed consent**	X						
**Inclusion and non-inclusion criteria**	X						
**Allocation**		X					
**Interventions**							
**Control group**			X				X
**Experimental group**			X				X
**Assessments**							
**Clinical data**			X				
**Pain intensity (NRS scale)**			X	X		X	X
**Dose of analgesics**			X	X			
**Postoperative complications (POMS)**				X	X		
**Vital status**						X	X

#### Sample size {14}

Given the fact that immediate postoperative pain can affect 30% of patients [1], a total of 161 patients per group (322 patients) will give 90% power using a bilateral test with a *p* value of 5% to detect a 50% reduction in the incidence of immediate postoperative pain (NRS ≤ 3) in patients guided by ANI. Given the specific features of this protocol (essentially the direct transfer from operating theater to continuous monitoring or ICU, use of continuous vasopressors), the final decision is to include a total of 380 patients (190 per group). An interim analysis will be scheduled halfway through the enrolment period (95 patients per group). The *p* value used to decide withdrawal from the trial on efficacy grounds is set at 0.003 (correction of the O’Brien-Fleming alpha-spending function).

#### Recruitment {15}

Participating centers, Clermont-Ferrand University hospital (primary site), Pierre Oudot Hospital Center, and Maisonneuve-Rosemont Hospital, have been chosen for their sufficient number of surgical cases and the knowledge of investigators in ANI-guided remifentanil administration. To achieve a fast and easy enrollment, a dedicated password-protected website (Research Electronic Data Capture, RedCap^®^, Nashville, TN, USA) will be used to register consent, inclusion, and randomization.

### Assignment of interventions: allocation

#### Sequence generation {16a}

Randomization will be performed over the REDCap^®^ website (https://redcap.chu-clermontferrand.fr) to allow immediate allocation. The randomization list is balanced by blocks of variable and undisclosed size and stratified per center and per type of surgery. Patients will be randomized at day 0, after written informed consent is obtained and just before surgery. Each patient will be given a unique patient number and a unique randomization number. It is not possible to change group after randomization.

